#### Patient satisfaction

Survey data on patient satisfaction are available in a form that reports the percentage of patient respondents who provided a positive response to a survey question item. Further, responses are available for individual question items and for 'dimensions,' related question items aggregated into groups that probe a particular concept or construct. Rates of positive responses from intervention and control team patients will be tabulated; measures of association will be calculated; generalized estimating equations will adjust for cluster randomization.

#### Paging activity

Recent research has suggested that hospital paging systems can be problematic. Paging activity can be highly interruptive. Calls to staff are often clinically inappropriate or not urgent enough to justify a necessary quick callback [33]. Paging can be disruptive to patient care [34] and scheduled rounds [35,36]. Disruptive pages may cause medical errors [37].

If the intervention is implemented correctly, face-to-face communication could increase in frequency and effectiveness. By implication, we suggest that there is potential for reductions in paging activity within and between members of GIM professions.

Administrative records will permit us to examine the total number of pages placed to paging devices of staff members of intervention and control teams, and the number of pages marked as urgent. Numbers of pages to intervention or control teams will be standardized by the number of individuals who carry pagers in the groups. Intervention-control group differences will be examined with linear mixed models.

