### Objectives: hypotheses

The SCRIPT Programme aims to create a cultural shift in the way health professionals communicate and collaborate in GIM hospital teams. There are three objectives for the SCRIPT Programme, the first two of which have been successfully completed. They are:

1. To assess interprofessional communication and collaboration;

2. To create an intervention – a tool or other process – that improves interprofessional communication and collaboration;

3. To implement and evaluate the effects of the intervention on outcomes.

The objective of the trial is to implement and evaluate the effects of an intervention aimed at enhancing collaborative communication between professionals and improving patient-centred care.

The research hypotheses for trial-related quantitative outcomes are:

1. Patients who are discharged from intervention teams will be less likely to be readmitted to hospital than patients discharged from control teams;

2. Mean time to readmission will be longer for patients discharged from intervention teams than for patients discharged from control teams;

3. Patients who are cared for by intervention teams will have shorter mean lengths of stay than patients in control teams;

4. Survey-measured perceptions of interprofessional collaboration will be higher among staff members of intervention teams than staff members of control teams;

5. Patients will report higher satisfaction with care after being treated by intervention teams than by control teams;

6. There will be an association between the number of calls to staff members' paging devices and team status; intervention-team staff members will receive fewer pages;

7. Adherence rates to evidence-based best practices for prescription drug therapy of geriatric acute-care inpatients will be greater among intervention teams than control teams.

Qualitative data are not collected in confirmation or denial of a hypothesis, but in explanation of the findings of the intervention trial. These data will be used to understand staff perceptions of the effects of the intervention and the barriers and catalysts for its implementation.

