In some of the hospital sites nursing and other health professionals' responsibilities require them to work on both intervention and control group teams; in these sites the survey instrument will direct survey respondents of these groups to self-select the team they work with most often from a complete list of the site's four GIM teams participating in the trial.

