#### Paging activity

For investigations of paging activity, potential subjects are GIM staff members who carry and use a hospital paging device. Development of a paging activity dataset will require assistance from two key resources: (1) GIM administrative functions that can identify GIM team members who carry pagers, and (2) reporting functions in a hospital site's information and communications technology division that can generate analytic reports of pages placed to GIM team members.

Administrative assistants in the hospital sites' Departments of Medicine will provide on-call schedules for medical staff members. On-call medical staff members carry pagers to provide coverage in various positions in the Department of Medicine, including GIM. Patient care managers in GIM teams will identify for us members of their team's nursing and allied health staff who carry paging devices.

After we have obtained the required information to identify individuals and positions in GIM that carry pagers, we will approach information technology reporting functions with the information. When we supply titles of GIM positions that carry pagers and paging identification numbers assigned to them, information technology staff is able to generate reports that can be used to determine the number of pages received by a specific paging identification number, and some other important characteristics of pager calls, chiefly, their designation as urgent or normal.

Recently we undertook exploratory conversations with members of two hospital sites' information technology divisions. Our goal was to probe the general character of paging records (i.e., data fields, content, frequency) that might be available for research use. These conversations suggested two key factors for consideration. First, while the nature of the request and the use of the data or reports in which the data routinely appear would be unusual, it is possible to generate time-delimited reports of activity on a selectively targeted group of paging devices. The second factor we learned is that there is a possibility that calls to paging devices can contain patient health information or other identifying information, and this information could also appear in administrative records of paging activity.

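### Dividing total pages by the number of pager carriers does not measure exposure, and no rule says which arm is credited with pages to carriers who work in both arms

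*Protocol article*

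**What the plan says.** Hypothesis 6 (Objectives: hypotheses) reads: "There will be an association between the number of calls to staff members' paging devices and team status; intervention-team staff members will receive fewer pages".

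The numerator is fixed under Statistical methods, Paging activity, as "the total number of pages placed to paging devices of staff members of intervention and control teams, and the number of pages marked as urgent". The same paragraph fixes the denominator: "Numbers of pages to intervention or control teams will be standardized by the number of individuals who carry pagers in the groups". Arms are then compared with linear mixed models. The rationale given there is that face-to-face contact may replace some calls, so that "there is potential for reductions in paging activity within and between members of GIM professions".

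Under Outcomes: measurement, Paging activity, reports are to be drawn by GIM position title and paging identification number, and on-call schedules are to be obtained. The requested fields are the receiving device, its assigned role, date and time, urgency and, where possible, the caller's number and role.

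Under Collaboration survey data, the article says that at some sites "nursing and other health professionals' responsibilities require them to work on both intervention and control group teams". These staff choose the team they work with most often, but that instruction is given for the survey only. The Covariates section also describes staff who work across several teams or units.

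**The concern.** Two features of the stated measure do not fit the data it will be computed from.

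First, a pager position generates calls over the time it is staffed, whoever holds the device. Dividing by people makes the rate depend on how many individuals passed through the position. The Intervention section expects two rotations of staff and resident physicians in the eight weeks. Participants and setting says non-physician staff may be full-time, part-time, temporary or casual. Teams with identical paging can therefore get different rates.

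Second, randomization is within hospital, two teams to each arm. Staff shared between teams at a site can therefore straddle the contrast being tested. The paging sections give no rule for placing their pages.

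At stake is a secondary outcome that the Discussion singles out as one of two addressing novel hypotheses. A real fall in paging could be blurred, and a difference between teams could partly reflect how carriers were counted.

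**Working it through.** The article gives no paging rate, variance, effect size or power for this outcome, so there is no figure to reproduce. The arithmetic below illustrates the mechanism on assumed values.

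**1. Denominator.** Take 100 pages (assumed) to one position over the intervention period, and let k be the number of individuals counted as carriers.

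Pages per carrier = 100 / k

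- k = 1: 100
- k = 1.5: 66.7
- k = 2: 50

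Paging is the same in all three cases. With coverage time as the denominator, eight weeks of continuous cover is 8 × 7 = 56 device-days. The rate is then 100 / 56 ≈ 1.8 pages per device-day for every k.

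The article does not say whether successive holders are all counted or only those carrying a pager at one time. The halving applies if two holders in turn are both counted. Counting only concurrent carriers would remove that effect, but would still treat a part-time carrier as equal to a full-time one.

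**2. Carriers who work in both arms.** Let r be the true relative reduction in pages on intervention-team work, and s the share of each arm's carriers who split their time equally between arms. Set the control rate at 1. A shared carrier's rate is 1 − r/2 whichever arm is credited.

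- Intervention mean: I = (1 − s)(1 − r) + s(1 − r/2)
- Control mean: C = (1 − s) + s(1 − r/2)
- Observed reduction: 1 − I/C

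With r = 0.20 (assumed):

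| s (assumed) | I | C | Observed reduction |
|---|---|---|---|
| 0 | 0.800 | 1.000 | 20% |
| 0.25 | 0.600 + 0.225 = 0.825 | 0.750 + 0.225 = 0.975 | 15.4% |
| 0.50 | 0.400 + 0.450 = 0.850 | 0.500 + 0.450 = 0.950 | 10.5% |

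**3. Can existing provisions absorb this?** The ward-basing covariate is a team-level indicator, so it cannot place an individual shared carrier's pages in an arm. The nursing workload covariates do not measure how long a pager was covered. The self-selection item identifies a survey respondent's main team but does not split that person's pages.

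**4. Are the data for a better measure available?** Device, role, date and time are requested for every page, and on-call schedules are to be obtained for medical staff. The analysis paragraph describes total and urgent counts only and plans no use of the time field.

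**The case against.** The strongest objection is that the outcome already matches its hypothesis. Hypothesis 6 concerns pages received by intervention-team staff and sets no limit on who placed them. A reader might infer from the rationale that only calls among GIM professions should count, and that a total count therefore fails the hypothesis. The documents do not support that. The rationale is a suggestion about mechanism, and total pages is a legitimate measure of interruption, which Potential benefits also names. Restricting the outcome to GIM-originated calls would change the estimand and would rest on a caller field requested only where possible.

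A reader might also infer that much non-GIM work is counted, because "On-call medical staff members carry pagers to provide coverage in various positions in the Department of Medicine, including GIM". That sentence can mean that on-call staff as a group fill various positions. Since reports are drawn by GIM position title and paging number, some filtering is already built in. It would be wrong to say that team paging cannot be isolated.

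Three further points stand. The article does not say that the staff who work in both arms carry pagers. It says that some nursing and allied staff do, and that managers list them by team. Physician rotation should be broadly similar across arms, given that regular rotation is an eligibility criterion and allocation is two-and-two within hospital. And nothing in the documents anchors the share of carriers affected.

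It is also fair to say that an article may leave operational rules for a secondary outcome to a fuller document. That covers the missing rule for shared carriers in part. It does not cover the denominator, which the article states outright.

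**Conclusion.** The point holds in a limited form. The head-count denominator is a stated choice and a poor measure of exposure. Counting two holders instead of one halves a position's rate with no change in paging. With randomization within hospital, the consequence is mainly added noise and chance imbalance across 20 teams, and not a systematic bias in one direction.

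The dilution from carriers who work in both arms is conditional. If such staff carry pagers and divide their time equally, a true 20% reduction would appear as about 15.4% with a quarter of carriers shared and 10.5% with half. The 20%, the shares and the equal split are all assumptions, and the true loss could be negligible at sites where carriers serve one team.

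Paging is a secondary outcome, and the readmission analysis is untouched. The change is worth making because the better measure uses data already being requested.

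**What to change.** In Statistical methods, Paging activity:

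- Keep total pages received, and urgent pages received, as the outcome, in line with hypothesis 6.
- Replace the number of carriers with device-days (or device-hours) of coverage of a GIM team position, derived from the device, role, date and time fields and the on-call schedules.
- Count only pages received while the device covers a single participating team. Report devices serving both arms separately, without crediting them to either arm.
- Where the caller's role is recorded, add GIM-originated pages as a supportive analysis.

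The cost is some extra linkage of paging records to schedules, and fewer pages in the main comparison. At sites where many carriers are shared, the result would describe single-team devices only, and the separate report should make that visible.

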#### Prescription drug therapy

Our hypotheses about clinical indications and prescription drug use in GIM are motivated by beliefs that communicative and collaborative improvements in health care can be related to optimal drug therapy. There are four hypotheses to be tested. First, 'is continuity of patient drug therapy greater among patients of intervention teams than control teams?' This question can be investigated by determining whether a patient fills a prescription after discharge for a drug that was used before GIM admission.

A second hypothesis will examine whether admitted patients received evidence-indicated drugs for every diagnosis they were known to have while receiving care in GIM teams. The third and fourth hypotheses are subsets of the second. The third hypothesis focuses specifically on problems that were not responsible causes for admission to the GIM division. We suggest that drug therapies for these problems will not be physicians' foremost priorities in the care plan; hence, improvements in interprofessional care could be most likely to be detected in increased rates of drug therapies for these problems. The fourth hypothesis will investigate uses of drugs that are contraindicated among elderly patients [26]. Usually, GIM patients are elderly.

Response variables related to the hypotheses will binary coded. Effects of intervention and control team statuses will be compared with generalized estimating equations.

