#### Prescription drug therapy

We will examine an outcome measure originating in the evidence-based medicine paradigm. Clinical evidence-based guidelines exist [26] to support appropriate uses of drugs for treatment of diseases commonly seen in GIM patients: diabetes, community acquired pneumonia, congestive heart failure, hypertension, asthma, chronic obstructive pulmonary disorder, stroke, and acute myocardial infarction. A database exists that can be used for investigation of adherence to evidence-based prescribing practices. This database is used in the Ontario Drug Benefit (ODB) program.

For defined groups of individuals, the Ontario Ministry of Health and Long-Term Care covers most of the cost of prescription drug products listed in the ODB formulary. Importantly for our purposes, one of these groups is Ontario residents 65 years of age and older. For drug products prescribed by an authorized Ontario prescriber, the ODB program covers approximately 3,000 prescription drug products.

The ODB program pays for listed drug products for individuals eligible for ODB coverage if the drugs are purchased in an Ontario pharmacy that is on-line with the ministry's Health Network or from an Ontario doctor licensed to sell prescription drug products. In 2004–2005, 70% of ODB beneficiaries were age 65 or older. It is likely that a majority of patients admitted into and discharged from GIM wards in the participating hospital sites are in this age group. We believe that many are eligible beneficiaries under the ODB program and that a large share of their post-65 prescription drug use history will exist in databases of the ODB program.

For analyses of prescription drug therapy, subjects are patients who are admitted to GIM divisions of participating hospital sites on or after the start date of the intervention at the site, and who are discharged to home from the GIM division on or before the last day of the next full month that follows the conclusion date of the intervention period. We will construct an ODB record for these patients that extends for 60 days after their date of discharge.

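### Stopping a contraindicated pre-admission drug can count against the intervention under drug hypothesis 1 and for it under drug hypothesis 4

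*Protocol article*

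**What the plan says.** The protocol article sets out four drug hypotheses under Statistical methods, Prescription drug therapy.

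- Hypothesis 1 asks: "is continuity of patient drug therapy greater among patients of intervention teams than control teams". Its measure follows: "This question can be investigated by determining whether a patient fills a prescription after discharge for a drug that was used before GIM admission". Neither sentence limits the drugs by class, indication or reason for stopping.
- Hypothesis 2 concerns receipt of evidence-indicated drugs for each known diagnosis. Hypothesis 3 narrows this to problems that did not cause the admission.
- Hypothesis 4: "The fourth hypothesis will investigate uses of drugs that are contraindicated among elderly patients". The section adds: "Usually, GIM patients are elderly".
- On how they relate: "The third and fourth hypotheses are subsets of the second".
- On coding: "Response variables related to the hypotheses will binary coded". The article does not say whether the unit is the drug or the patient, or whether one refilled drug is enough.

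Under Objectives: hypotheses, the trial-level drug hypothesis reads: "Adherence rates to evidence-based best practices for prescription drug therapy of geriatric acute-care inpatients will be greater among intervention teams than control teams". Under Outcomes: measurement, Prescription drug therapy, the follow-up for fills is given: "We will construct an ODB record for these patients that extends for 60 days after their date of discharge". The Discussion names continuity before and after the hospital stay as one of two measures that can help test novel hypotheses.

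**The concern.** Hypothesis 1 has a printed direction (more fills are better) and a printed measure that treats all pre-admission drugs alike. Hypothesis 4 singles out some drugs for which fewer fills are the good result. A drug can belong to both sets, and for such a drug the two endpoints reward opposite outcomes.

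This matters because drug review is a plausible route of benefit for this intervention. Staff are asked to share profession-specific issues and to invite the other profession's concerns, and pharmacy is listed among the common professions on a team. If better collaboration leads teams to stop more drugs on the contraindicated list, continuity falls for that reason alone. A flat or adverse continuity result could then partly reflect what hypothesis 4 counts as better care, and a favourable one could partly reflect listed drugs being carried on.

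Calling hypothesis 4 a subset of hypothesis 2 adds to the confusion. Avoiding contraindicated drugs is not part of receiving indicated ones, and the favourable direction is reversed.

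**Working it through.** The article gives no rate, power or effect size for any drug outcome, so there is no figure to reproduce. The check is a coding exercise, followed by an illustration on assumed inputs.

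**Step 1. Code one event under both hypotheses.** Take a drug used before admission that is on the contraindicated list.

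| What happens to the drug | Hypothesis 1 (fill is success) | Hypothesis 4 (use is failure) |
|---|---|---|
| Stopped, no fill after discharge | unfavourable | favourable |
| Carried on, filled after discharge | favourable | unfavourable |

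The direction in the last column is not written in hypothesis 4's own sentence. It follows from the trial-level hypothesis of greater adherence to best practice in intervention teams, and from the stated motive of optimal drug therapy.

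**Step 2. Do the same patients feed both?** Largely yes. The section calls the patients usually elderly, the trial-level hypothesis is about geriatric inpatients, and the claims source is chosen because it covers residents aged 65 and over.

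**Step 3. Does another section narrow the measure?** No. The measurement section adds only the 60-day record, and the Discussion repeats continuity without qualification.

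**Step 4. Size if the unit is the drug (assumed inputs).** Let *c* be the share of pre-admission drugs that are contraindicated and *g* the extra share of these that intervention teams stop. Other drugs are refilled equally in both arms. The shift in continuity is −*c* × *g*.

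- *c* = 5%, *g* = 10 points: −0.05 × 10 = −0.5 points
- *c* = 10%, *g* = 20 points: −0.10 × 20 = −2.0 points
- *c* = 30%, *g* = 40 points: −0.30 × 40 = −12.0 points

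**Step 5. Size if the unit is the patient (assumed inputs).** Each patient has *k* drugs, one of them contraindicated and stopped in 20% of control and 50% of intervention patients. Each of the others is refilled with probability 0.85, independently.

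- All-drugs rule: 0.85^(k−1) × (1 − stop rate)
- Any-drug rule: 1 − 0.15^(k−1) × stop rate

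| *k* | All drugs: control vs intervention | Any drug: control vs intervention |
|---|---|---|
| 1 | 80.0% vs 50.0% | 80.0% vs 50.0% |
| 3 | 57.8% vs 36.1% | 99.6% vs 98.9% |
| 5 | 41.8% vs 26.1% | 99.99% vs 99.97% |

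The shift is adverse to the intervention in every cell. It is large under the all-drugs rule and close to nil under the any-drug rule once a patient takes several drugs.

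**Step 6. With listed drugs removed from the denominator.** At *k* = 3, two drugs remain. The all-drugs rule gives 0.85² = 72.3% in both arms, and the any-drug rule gives 1 − 0.15² = 97.8% in both arms. The artefact disappears. At *k* = 1 the patient has no eligible drug and leaves the measure.

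**The case against.** **The coding rule is not fixed.** The measure is worded tentatively, about a patient and a drug. A reader might infer that every pre-admission drug left unfilled is scored as a failure, but the article does not say that. Under an any-drug rule, a patient whose listed drug is stopped but who refills another is still a success, and the conflict is confined mainly to patients with few other drugs. This stands. It limits the size of the problem without removing it, and the any-drug rule has its own cost: with several drugs per patient, continuity sits so near 100% that it could hardly show a benefit.

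**The rates are assumed.** This also stands. Inputs can be chosen so that gains on appropriate drugs and stops of listed drugs cancel exactly, but that shows only that a misleading null is possible. The documents give no basis for predicting one.

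**A condensed article leaves such rules to the full plan.** This is fair for drug lists, short courses, days' supply and grace periods, and their absence is not held against the plan. The point here rests on what is printed: a direction and an unrestricted measure that conflict with the companion hypothesis.

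**The hypotheses are tested separately.** Reporting both would let a reader see continuity and contraindicated use fall together. That helps interpretation, but it does not show how much of any continuity change comes from listed drugs.

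**The 60-day record.** A reader might infer that patients still holding a longer supply will be miscoded as having stopped. The documents do not support that as a finding. They give no supply lengths and do not say that earlier dispensing will be ignored. Any such error should be similar in both arms and would mainly dilute the comparison.

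**Conclusion.** The conflict is real and is in the printed text: hypothesis 1 exempts no drug, hypothesis 4 implies that less use of some of the same drugs is better, and no other section reconciles them. It rests on one inference, the favourable direction of hypothesis 4, which the trial-level hypothesis supports well.

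Its size cannot be derived from the article. On assumed inputs it runs from a negligible shift (any-drug rule, several drugs) to 12 points per drug, or about 22 points per patient (57.8 − 36.1 = 21.7, all-drugs rule, three drugs). The largest illustrated gap is 30 points, for a patient whose only drug is on the list.

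Continuity is one of four hypotheses beneath a secondary outcome. A reader might take the Discussion's emphasis to mean that the trial's main conclusion is at risk. It is not: the primary readmission outcome and the sample size are unaffected. The definitions should still be reconciled before the drug data are analysed, because exclusions chosen afterwards would look selective.

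**What to change.** Reconcile the two definitions as a matter of endpoint coding. No prescribing rule is implied.

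1. Restrict the hypothesis 1 denominator to pre-admission drugs that are not on the contraindicated list already planned for hypothesis 4, and preferably to drugs in chronic use.
2. Set eligibility from pre-admission records only. What is prescribed after randomisation may be affected by the intervention, and a denominator that depends on it can bias the comparison.
3. For the same reason, count a switch within a drug class as continued and do not exclude the switched drug.
4. State hypothesis 4 as a separate endpoint with its own direction (less use is favourable), not as a subset of hypothesis 2.
5. State the unit and, if it is the patient, the any-drug or all-drugs rule.
6. If wanted, treat the length of the post-discharge record as a sensitivity check only.

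The cost is wording, plus flagging listed and chronic-use drugs in claims data already to be obtained. The downside is that fewer drugs enter the continuity measure, and patients whose only pre-admission drugs are on the list drop out of it, so precision falls somewhat. Direction of benefit becomes clearer but not perfect, since claims data do not show why other drugs were stopped.

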#### Covariates

Model-based estimates of intervention effects on the outcomes of readmission, length of stay, use of optimal drug therapy, patient satisfaction, and use of paging devices will employ patient-level and team-level covariates. Patient-related factors to be controlled will be patients' age and gender.

Other covariates will be measures of hospital health care processes hypothesized to be related either to outcome measures or to intervention uptake. The intervention's focal concern is the improvement of interprofessional performance of GIM teaching teams. Therefore, we propose to use the following constructs as structural indicators of functional team processes of care:

• *Ward-based assignment of medical, nursing, and allied health professional staff*. 'Ward basing' refers to hospital practices specifying the deployment of healthcare staff members to a single physical ward location. This arrangement is in contrast to assignments that have staff members working among different medical teams or nursing units as they treat patients. For example, if nurses and nursing units are fixed to physical ward locations, then medical team and professional health staff members could be assigned to patients in such a way that they are required to work with members of several different nursing units. If so, they are said to 'cross teams or units.' On the other hand, if medical teams are fixed to physical ward locations, then it is possible that nurses and professional health staff could be required to work among multiple different medical teams. It is also possible that both medical teams and nursing units are given fixed assignments to single ward locations and professional health staff are assigned to work across multiple combinations of medical teams and nursing units. All of these configurations create variation in the degree to which GIM staff are consolidated to work in one physical location.

Work assignments that see GIM staff consistently – and as a matter of hospital policy – working in multiple physical locations, where work colleagues are more likely than not to be unfamiliar, might have negative impacts on achievement of effective interprofessional collaboration and patient outcomes. An indicator variable will be developed to code whether clinical teaching teams are organized to consolidate interprofessional teams and team members to a single physical ward location.

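### Drug hypotheses 2 to 4 adjust at patient level only for age and gender, although the pre-admission drug history that hypothesis 1 requires could serve as a baseline covariate

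*Protocol article*

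**What the plan says.** The Prescription drug therapy part of Statistical methods sets four hypotheses. The first is continuity, judged by "whether a patient fills a prescription after discharge for a drug that was used before GIM admission". The second is receipt of indicated drugs for all known diagnoses. The third is the same for problems that did not cause the admission. The fourth is use of drugs contraindicated in the elderly. On coding and analysis it says "Response variables related to the hypotheses will binary coded" and "Effects of intervention and control team statuses will be compared with generalized estimating equations".

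The Covariates section says that models for "use of optimal drug therapy, patient satisfaction, and use of paging devices will employ patient-level and team-level covariates". It then fixes the patient level: "Patient-related factors to be controlled will be patients' age and gender". The team-level constructs are ward basing, discharge planner, time in interdisciplinary rounds, nursing staff characteristics and nursing workload. None of them uses a patient's earlier drug use.

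Under Outcomes: measurement, the drug data come from the Ontario Drug Benefit (ODB) program. For eligible older patients the authors expect that "a large share of their post-65 prescription drug use history will exist in databases of the ODB program". The record they will build runs to 60 days after discharge.

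**The concern.** For a long-term drug, whether a patient fills it after discharge depends heavily on whether the patient was taking it before admission, which the team did not choose. Prior use precedes the intervention, so adjusting for it is safe. Hypothesis 1 cannot be tested without it, so the plan must obtain it anyway. Yet the article's list of patient-level covariates leaves it out of the models for hypotheses 2 to 4.

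What is at stake is precision. With ten teams per arm, a chance difference between arms in prior use passes into the estimated effect, and age and gender are unlikely to remove much of it. This matters most for hypothesis 3, where the article itself expects an effect to be easiest to detect. Problems that did not cause the admission are often long-standing, so prior status can often be defined for them.

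**Working it through.** **The plan's own figures.** The article gives no power, prevalence or ICC for any drug outcome. Its readmission powers reproduce. The design effect is 1 + 199 × 0.01 = 2.99 and the effective n per arm is 2000/2.99 = 669. Two-sided 5% power is then 93.6% for 10% v 5% (stated 93%) and 67.3% for 5% v 2.5% (stated 67%). This does not bear on the drug models, so everything below rests on assumptions.

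**Inputs.**
- From the article: 20 teams, 10 per arm (two per arm in each of five hospitals). The readmission ICC of 0.01 is borrowed for illustration.
- Assumed: m = 100 patients per team with usable drug-benefit data, so 1000 per arm; an ICC of 0, 0.01 or 0.05 for the drug outcome.
- Assumed strong case: 25% use a contraindicated drug before admission, 75% of users continue, 4% of non-users start.
- Assumed weak case: 30% use, 50% continue, 10% start.

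**Step 1: correlation between prior and later use.** With p = prior use and q = later use, φ = (P(both) − pq) / √[p(1−p)q(1−q)].
- Strong: q = 0.25 × 0.75 + 0.75 × 0.04 = 0.2175. φ = (0.1875 − 0.25 × 0.2175) / √(0.25 × 0.75 × 0.2175 × 0.7825) = 0.745, so φ² = 0.555.
- Weak: q = 0.30 × 0.50 + 0.70 × 0.10 = 0.22. φ = (0.15 − 0.30 × 0.22) / √(0.30 × 0.70 × 0.22 × 0.78) = 0.44, so φ² = 0.196.

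**Step 2: no clustering.** The variance cut equals φ²: about 56% or 20%. In the strong case the unadjusted SE of the risk difference is √(2 × 0.2175 × 0.7825/1000) = 0.0184. Adjusted, it is 0.0184 × √(1 − 0.555) = 0.0123.

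**Step 3: teams differ in what they newly prescribe.** Prior use cannot explain that part of the variance. The variance is proportional to 1 + (m−1)ρ = (1−ρ) + mρ, and adjustment removes φ² of the (1−ρ) part only. The cut is therefore (1−ρ)φ² / [1 + (m−1)ρ].

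| ICC | Strong, formula | Weak, formula | Simulation, strong / weak |
|---|---|---|---|
| 0 | 56% | 20% | about 56% / 20% |
| 0.01 | 0.99 × 0.555/1.99 = 28% | 0.99 × 0.196/1.99 = 10% | about 27% / 8% |
| 0.05 | 0.95 × 0.555/5.95 = 9% | 0.95 × 0.196/5.95 = 3% | about 10% / 3% |

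Formula and simulation agree within about two points. At an ICC of 0.01 the strong-case SE goes from √(2 × 0.2175 × 0.7825 × 1.99/1000) = 2.6 points to 2.6 × √(1 − 0.276) = 2.2 points.

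**Step 4: teams already differ in pre-admission use.** A second simulation (20 teams of 100, 50% prevalence, the same team differences before and after, larger team variation) gave a standard deviation of the estimated effect of 4.78 points unadjusted and 3.69 adjusted. The prior/later correlation was only 0.29. The variance cut is 1 − (3.69/4.78)² = 40%, well above 0.29² = 8%, because prior use then also carries the team difference. Both estimators averaged close to zero when no effect was simulated, so neither was biased.

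**The case against.** The strongest case on the other side is that nothing here is an error. This is one part of a secondary outcome in a condensed article, the comparison is randomized, and outcome-specific covariates and look-back windows are often left to an analysis plan. That stands as far as it goes: this is an improvement, not a defect that invalidates an analysis. But the article does not leave the patient-level covariates open. It names them, and prior drug use is not among them.

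A reader might also infer four stronger things that the document does not support.
- *That the models adjust for age and gender alone.* They do not; the Covariates section adds team-level factors for drug therapy.
- *That every patient has a baseline value of the same outcome.* The listed conditions include community acquired pneumonia, stroke and acute myocardial infarction. A diagnosis first made at the index admission has no earlier indicated-drug status. Drug-benefit history is also incomplete, and short for those who have just turned 65.
- *That hypotheses 2 to 4 are expressly defined by fills after discharge.* Only hypothesis 1 is. For the others this is inferred from the data source and its 60-day window, while hypothesis 2 is worded around drugs received by admitted patients.
- *That the omission biases the result, or that about half the variance is always recoverable.* Randomization protects against bias. The 56% figure is the strong case with no clustering, and it falls sharply if teams differ in new prescribing.

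**Conclusion.** The point holds as a low-cost gain in precision. The patient-level covariates for hypotheses 2 to 4 are age and gender only, while pre-admission drug use, which hypothesis 1 obliges the trial to obtain, goes unused in those models. The loss is in precision and in protection against chance imbalance across 20 teams; there is no bias.

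For hypothesis 4 the plausible variance cut runs from about 3% (weak persistence, ICC 0.05) to about 56% (strong persistence, no clustering). It is about 8% to 27% at an ICC of 0.01, and higher if teams already differ in prior use. The prevalences, persistence rates, patients per team and drug-outcome ICC are all assumed. No figure was worked out for hypotheses 2 and 3, where the gain is limited to conditions that existed before admission. The conclusion also depends on these outcomes being read from post-discharge fills.

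**What to change.** In Statistical methods, under Prescription drug therapy and Covariates:

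1. Add the patient's pre-admission status on the same measure, taken from a fixed look-back in the drug-benefit file, as a patient-level covariate in the generalized estimating equations. For hypothesis 4 this is whether a contraindicated drug was filled. For hypotheses 2 and 3 it is whether the indicated drug was filled for conditions that existed before admission.
2. Give a separate category to diagnoses new at the index admission and to patients with no available history, so that nobody is dropped.
3. State whether hypotheses 2 to 4 are scored from post-discharge fills.
4. The gains above are for the risk difference. If a logit link is used, the coefficient becomes conditional on prior use, so report a standardized risk difference as well.

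The cost is analysis wording, one or more derived variables and a rule for missing history. The source data are those that hypothesis 1 already needs, and no trial procedure changes.
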